## 7 STUDY TREATMENTS

### Description of the Investigational Medicinal Product

#### Description of Standard Care

The standard care will follow the best practice for the type, severity and stage of ulcer for each participant. This will be at the investigator's discretion. Details of the standard care will be recorded.

#### IP Storage, Handling and Preparation

IP will be prepared by [name] in accordance with the Investigator Brochure. Bottles of IP/saline will be stored in the Basil Hetzel Institute building clinical trial room 2, labelled with study ID. Bottles will be used to soak gauze for rinsing the wound of each participant according to their study ID and the protocol.

#### IP Administration and Post-Dose Monitoring

Only participants enrolled in the study may receive study treatment. The Principal Investigator (PI) or authorised designee will ensure that the study treatment at site is safely handled in compliance with requirements. The PI is responsible for ensuring that the study treatment is dispensed in accordance with the protocol and only to participants enrolled in the study.

#### Criteria for Postponing or Stopping Study Treatment

##### *Prior to the Application of Treatment*

The treatment should not be applied if, in the opinion of the Investigator, there is a risk that the participant will be unable to tolerate treatment for any reason.

Treatment applications should be deferred if probable ulcer infection is noted. If treatment is deferred the patient can re-enter the trial at the point at which they left once the problem settles and at the Investigator's discretion.

Under these circumstances, at the discretion of the Investigator, study treatment may be postponed and initiated at a later time, provided that:

- The problem that resulted in postponement of the study treatment resolves, and is not considered by the Investigator to be likely to recur; AND
- The relevant visit is still expected to be completed within the stipulated visit window.

Alternatively, the participant may be withdrawn from the study.

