1. PAW
2. Control (sterile saline)

Participants will receive the appropriate rinse, applied to gauze as a temporary dressing, for ten minutes during a clinic appointment.

**Design:** A randomised, controlled, prospective trial. Participants will be patients with DFU.

**Blinding:** All clinical personnel and all participants will be blind to the assignment and treatment administered (double-blind). Only [name] will retain knowledge of treatment based on preparation of treatment and linkage on a spreadsheet with study ID. This spreadsheet will be used to match for study safety and efficacy on end of study, and/or once an SUSAR has been confirmed.

**Screening and Randomisation:** Participants who provide consent to participate in the study and meet all eligibility criteria and no exclusion criteria will be randomly assigned to one of the two groups.

**Treatment and Evaluation Period:** Participants will attend a total of 12 scheduled visits over 6 weeks, plus follow-up wound review visits fortnightly until week 12 and final visit at week 18.

A study flow diagram is provided in Figure 1.

[figure not shown]

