## **Withdrawal of Participants from Study**

Participants can terminate their study participation at any time and without giving a reason, without prejudice to further treatment. Participants who discontinue from the study will be asked about the reason(s) for their discontinuation only to determine the presence of any AEs. If possible and willing, they will be seen and assessed by an Investigator and have a final study visit. AEs should be followed up until resolved or stable and determined to be chronic.

Participants who withdraw from the study prior to the final scheduled visit will have the final visit procedures conducted at the time of withdrawal, if possible. If a participant withdraws due to the need for amputation of the foot/limb with the study ulcer, they will be asked to have the final visit procedures prior to the amputation, if possible.

If a participant withdraws due to the study wound being completely healed, they should have the final visit procedures.

On withdrawal, participants will have the opportunity to request that their existing data and samples be expunged from the study, to the extent it is possible to do so.

The Principal Investigator can exclude a participant from continuing in the study. Possible reasons for discontinuing a participant may include:

- Participant withdrawal of consent
- Inability to tolerate the study treatment
- Any unacceptable AEs, in the judgement of the Principal Investigator
- Participant's non-adherence to the protocol
- The use of another investigational research agent prior to Week 6 has been deemed necessary
- Termination of the study for administrative, financial, or other reasons.

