## **5 ADVERSE EVENTS**

Participants will be questioned and monitored throughout the study with regard to any adverse events (AEs) they may have experienced. An AE can therefore be any unfavourable and unintended sign (including an abnormal laboratory finding), symptom, or disease temporally associated with the use of a medicinal product, regardless of relationship to the medicinal (investigational) product.

Determinations of severity and causality of any AE can only be determined by a clinical Investigator without awareness of whether the treatment used is PAW or control.

An AE shall be classified as serious (a Serious Adverse Event, or SAE) if, in the opinion of either the Investigator or the Sponsor, it:

- Results in death.
- Is life-threatening, i.e., in which the participant was at risk of death at the time of the event.
- Results in permanent impairment of a body structure or body function
- Requires in-patient hospitalisation or prolongation of existing hospitalisation.
- Results in persistent or significant disability/incapacity.

Important medical events that are not immediately life-threatening and that do not result in death or hospitalisation may still be considered serious if, in the opinion of the Investigator, they jeopardise the participant or require intervention to prevent one of the other outcomes listed above. Such events should also be treated as SAEs.

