### *Assessment of Causality*

The Investigator must assess the causality of each AE and SAE. Assessing causality involves consideration of whether there is a reasonable possibility that the event may have been caused by the treatment.

- **Not related:** AE for which there is evidence of another explanation, e.g. the AE is obviously explained by the participant's disease(s), is in accordance with the known effect of a concomitant medication or has occurred prior to first administration of study treatment.
- **Unlikely related:** AE with a time to study treatment administration that makes a relationship improbable (but not impossible), and disease or other drugs provide plausible explanations.
- **Possibly related:** AE with a reasonable time relationship to study treatment administration, but which could also be explained by disease or other drugs.
- **Probably related:** AE with reasonable time relationship to study treatment administration that is unlikely to be attributed to disease or other drugs.
- **Definitely related:** AE with plausible time relationship to study treatment administration, which cannot be reasonably explained by the known characteristics of the participant's clinical state, environmental factors, or other modes of therapy administered to the participant.

All AEs must be documented by the Investigator, regardless of causality.

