#### *After the Application of Treatment*

Once dressing is applied, its application should be immediately removed if:

- in the opinion of the Investigator, a participant exhibits signs or symptoms of shock or an allergic reaction; OR
- in the opinion of the Investigator, a participant exhibits any other unacceptable AE that warrant its removal; OR
- if the participant requests its removal.

When a rinse dressing is removed, it should not be reapplied, and the time and date of removal should be recorded.

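### No safety event, not even a related death or a confirmed SUSAR, obliges a recorded study-level decision or a hold on randomisation and dosing in this first-in-human trial

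*Protocol*

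**What the plan says.** Section 7, under Criteria for Postponing or Stopping Study Treatment, has three parts that bear on this.

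- **Before application**, treatment "should not be applied if, in the opinion of the Investigator, there is a risk that the participant will be unable to tolerate treatment". Probable ulcer infection defers it. A postponed application may go ahead if the problem has resolved and "The relevant visit is still expected to be completed within the stipulated visit window"; otherwise the participant may be withdrawn.
- **After application**, the dressing comes off if "a participant exhibits signs or symptoms of shock or an allergic reaction", if "in the opinion of the Investigator, a participant exhibits any other unacceptable AE that warrant its removal", or if the participant asks.
- **Withdrawal of Participants from Study** (Section 3) lists reasons for discontinuing a participant. The last is "Termination of the study for administrative, financial, or other reasons", which names no safety event.

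Two provisions reach beyond the individual. Section 5 sends every SAE to the Sponsor within 24 hours, whatever its cause. The Blinding paragraph of Section 3 says of the allocation list: "This spreadsheet will be used to match for study safety and efficacy on end of study, and/or once an SUSAR has been confirmed". Section 5 also requires blinded rating: "Determinations of severity and causality of any AE can only be determined by a clinical Investigator", who must not know the allocation.

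**The concern.** The Risk/Benefit Assessment calls this a first-in-human trial and accepts that some risks cannot be foreseen. Table 1 in Section 2 makes safety and tolerability to 6 weeks the primary objective. A reader would expect such a protocol to name at least one event after which dosing of other participants waits for a decision.

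The section whose title promises stopping criteria stops at the individual. Each case can be handled exactly as written while the next participant is randomised and dosed, and no one has to record why it was right to go on. Blinded rating sharpens this. The Investigator judging one case does not know its allocation, so a pattern shows only if cases are looked at together.

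**Working it through.** **1. What each provision obliges.** The protocol states no stopping boundary, event rate or power figure to reproduce; Sample Size Assumptions says that no formal calculation was made. The first check is therefore textual.

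| Provision | Acts on | Study-level review or hold required? |
|---|---|---|
| Pig study completed first (Risk/Benefit Assessment) | Start of human dosing | No; it ends once dosing begins |
| Saline wash for pain (Risk/Benefit Assessment) | One application | No |
| Withhold, defer or withdraw (Section 7) | One participant | No |
| Dressing removal (Section 7) | One application | No |
| Discontinuation list (Section 3) | One participant; study termination mentioned without a safety trigger | No |
| Study doctor present at screening and week two at minimum (Section 4) | One visit | No |
| Contact dermatitis check (Section 6), bloods at two weeks (Section 4) | One participant | No |
| SAE to Sponsor within 24 hours (Section 5) | Information flow to the Sponsor | No |
| Allocation matching on a confirmed SUSAR (Section 3) | Unblinding for study safety | No |
| Site visits by the research office (Section 10) | Adherence and data accuracy; visits are optional | No |

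The SAP cannot fill the gap. Section 9 requires it to be final only before database lock, by which time dosing is over.

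**2. Unnecessary holds under a single-event trigger.** Inputs: 20 participants (Number of Participants), and an assumed probability q that a participant has a triggering event PAW did not cause, equal in both arms and independent between participants.

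P(at least one hold) = 1 − (1 − q)^20

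| Assumed q | Calculation | Result |
|---|---|---|
| 0.5% | 1 − 0.995^20 | 9.5% |
| 1% | 1 − 0.99^20 | 18.2% |
| 2% | 1 − 0.98^20 | 33.2% |
| 5% | 1 − 0.95^20 | 64.2% |

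The upper rows cannot be dismissed, because the possibly related grade covers an "AE with a reasonable time relationship to study treatment administration, but which could also be explained by disease or other drugs". The formula also counts events after the last planned application, when there is nothing left to hold, so it errs high.

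**3. Would a count of less severe events add much?** Take a hold at 3 participants, pooled over both arms, with a related SAE or a related treatment-stopping event. The chance of reaching 3 is the upper tail of the sum of two binomials with n = 10 each. For the reactors averted I simulated 200,000 trials, with these inputs:

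- 10 PAW and 10 control in random order.
- Starts 11.9 days apart: a 52-week study period less 18 weeks of participation leaves 34 weeks, and 34 × 7 / 20 = 11.9.
- Applications on the study days in the visit table (0, 7, 14, 28, 35, 42), with a reaction equally likely at each.
- Every hold assumed to become a permanent stop, which favours the rule.

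| Assumed PAW / control rate | Count of 3 reached | PAW reactors expected without a rule | Averted |
|---|---|---|---|
| 10% / 5% | 18.5% | 1 | 0.05 |
| 20% / 5% | 46.8% | 2 | 0.28 |
| 30% / 5% | 72.2% | 3 | 0.75 |

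With no PAW effect, the count is still reached in 7.5% of trials at 5% in both arms and in 32% at 10% in both arms.

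**The case against.** **The individual-level rules are correct for their purpose, and a halting rule may sit elsewhere.** The Investigator Brochure is not at hand, and Section 10 refers to regulations, GCP and site procedures whose content is not shown. This limits the finding to the protocol. It does not remove it: nothing in the text points to a halting rule in those places, and a rule that binds staff while they dose belongs where the stopping criteria are.

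**Oversight above the participant exists.** This stands. Matching allocation for study safety on a confirmed SUSAR is at least partly a study-level step, every SAE reaches the Sponsor quickly, and the study can be ended for other reasons. In a 20-participant trial at two hospitals, the people who would decide are likely to know of any grave case. A reader might infer from the gap that the trial has no safety oversight, or that dosing would carry on after a related death. The documents support neither. They show only that a pause and a recorded decision are left to discretion.

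**The expected risk is low.** The product is a ten-minute topical rinse, released for human use only after the pig study shows no ill effects. That lowers the chance of a trigger without settling what follows one.

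**Holds may often be unnecessary.** The Introduction says many of these patients go on to infection needing hospital care. Such an SAE, if rated related and confirmed as unexpected, could trigger a hold. This stands and is the main cost.

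**Conclusion.** The point holds as a gap in the protocol text. After a confirmed SUSAR or a related death, no provision shown requires a recorded study-level decision or holds randomisation and dosing. Up to 10 planned PAW participants, fewer those already dosed, could be exposed without one. This is a change the sponsor should make: it is inexpensive and protects participants in a trial whose primary question is safety.

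The conclusion rests on the wording and needs no event rate. The size of the downside does: about 10% to 64% of trials would have an unnecessary hold as the assumed rate runs from 0.5% to 5% per participant. The benefit of the single-event trigger cannot be sized from the documents.

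A reader might also infer that a count rule is required. It is not. A threshold such as 3 is a judgement that the documents do not supply, and its benefit is small at 10% to 20% even if every hold became permanent.

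**What to change.** Add a study-level paragraph to Section 7:

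- **Trigger:** any confirmed SUSAR, or any fatal or life-threatening event rated possibly, probably or definitely related.
- **Action:** randomisation and all further applications are held until the Principal Investigator and the Sponsor have reviewed all accumulated adverse events and recorded a decision to continue, change or stop.
- **Blinding:** the review uses blinded pooled data. Only the matched allocation of the SUSAR case may be disclosed, and to the Sponsor alone, so that the Investigators who rate causality stay blind.
- **Missed applications:** those missed because of the hold are recorded as such and do not by themselves make a participant non-evaluable under Replacement of Participants.

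The sponsor may add a pooled count of less severe related events, and if so should state its threshold and what does not count, such as mild transient discomfort.

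The cost is one amendment paragraph, with no new committee, procedure or participants. The price in conduct is the unnecessary holds shown above and some applications falling outside the three-day visit windows.

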### **Overview of Study Visits**

Study procedures should be performed at relevant study visits in accordance with the schedule of procedures outlined in Table 1. The Principal Investigator or other study doctor will be present for study treatment at screening and at the week two visit at minimum to ensure patient safety and observe for AEs.

Participants will only be enrolled and randomised to study treatment if they meet all eligibility criteria, and none of the exclusion criteria.

Study visits will be arranged at Royal Adelaide Hospital and/or The Queen Elizabeth Hospital, aligning with patient clinical visit scheduling where possible to minimise inconvenience to participants. A window of plus or minus three days is permitted for Visits 1 to 6, and a window of plus or minus seven days is permitted for follow-up Visits 7-10. Study visits via home visit are permitted for Visits 3-10.

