### *Recording of Adverse Events*

All AEs that occur from the time of informed consent until the participant completes or withdraws from the study will be recorded in REDCap.

SAEs deemed possibly, probably or definitely related to study treatment occurring after the participant completes the study will also be reported to the Sponsor, or delegate, if the Investigator becomes aware of them.

It is preferable that AEs are reported as diagnoses if one is able to be made, rather than individual signs and symptoms. The AE description, onset and resolution dates, severity, causality and outcome must be recorded, as well as any actions taken.

Unless a diagnosis is made, or signs and symptoms are present, laboratory values or vital signs abnormalities should only be reported as AEs if they cause the participant to discontinue from the study, the Investigator feels it is clinically significant, or they meet a criterion for a SAE.

If an AE leads to premature discontinuation of the study, the appropriate pages of REDCap must be completed.

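### After an infection deferral, the protocol is unclear on whether treatment may resume outside the 3-day visit window, and the only alternative it names, optional withdrawal from the study, would stop recording of new adverse events

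*Protocol*

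**What the plan says.** Protocol section 7, Prior to the Application of Treatment, requires deferral when probable ulcer infection is seen. It then says three things in sequence.

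- Return after deferral: "the patient can re-enter the trial at the point at which they left once the problem settles and at the Investigator's discretion".
- In the next paragraph, introduced as applying to the same circumstances, "study treatment may be postponed and initiated at a later time", on two joint conditions. The problem must have resolved and be unlikely to recur, and "The relevant visit is still expected to be completed within the stipulated visit window".
- The remaining option: "Alternatively, the participant may be withdrawn from the study".

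Section 4, Overview of Study Visits, sets the window: "A window of plus or minus three days is permitted for Visits 1 to 6".

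Section 5, Recording of Adverse Events, covers events from consent "until the participant completes or withdraws from the study will be recorded in REDCap". Its only later capture is of treatment-related serious events "occurring after the participant completes the study will also be reported to the Sponsor, or delegate, if the Investigator becomes aware of them".

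Section 3, Withdrawal of Participants from Study, asks for the final-visit procedures at the time of withdrawal where possible. For events already known it says: "AEs should be followed up until resolved or stable and determined to be chronic".

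Table 1 in section 2 sets the primary safety analysis on data up to 6 weeks from the start of treatment, and lists infection of the study ulcer among the secondary outcomes.

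**The concern.** An infection that takes a week or more to settle falls between the two paragraphs. The first appears to allow a return whenever the problem settles. The second appears to bar it once the window has passed. Two investigators could handle the same participant differently and each point to the same section.

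The second difficulty is the exit that the section names. It is withdrawal from the study, not from treatment. Nothing in the protocol describes stopping the rinse while staying in follow-up. If an investigator uses this exit, new adverse events in the rest of the 6-week period are not recorded, for a participant selected because of infection. The Risk/Benefit Assessment expects less recurrent infection on plasma-activated water, so on the trial's own hypothesis such exits could differ between arms. If the withdrawal counts as due to an adverse event, section 3, Replacement of Participants, does not allow the place to be refilled.

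A statistical analysis plan cannot repair this. It can describe missing data, but it cannot recover events that were never recorded.

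**Working it through.** The plan states no figure on this point, so the check is a side-by-side reading followed by day counts.

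**Reading the two paragraphs together**

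1. If the window condition qualifies the return sentence, the rules agree. But a return at the point of leaving then has almost no content, because someone seen within 3 days of the planned day has not left the schedule. Withdrawal is the only named route for a longer pause.
2. If the window condition applies only to starting treatment, as the word for initiation might suggest, a long mid-course pause is allowed and need not end in withdrawal. The text does not say this. The condition follows directly on the deferral sentences and refers to the relevant visit, not to Visit 1.
3. The text does not decide between these readings.

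**Inputs**

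- Primary safety period: 6 weeks = 42 days from Day 0 (section 2, Table 1).
- Visit 3: Day 14 in the schedule of procedures, window Days 11 to 17 (sections 4 and 3-day rule above). The schedule's listed days jump from 14 to 28, but Visit 3 is on Day 14 on a strict weekly calendar too, so the example does not depend on that gap.
- Arm size: 10 (section 9, Sample Size Assumptions). Arm total = 10 × 42 = 420 participant-days.

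**Days of new-event recording lost by one withdrawal linked to Visit 3**

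- Withdrawn on the planned day: 42 − 14 = 28 days; 28/42 = 67% of that participant's period; 28/420 = 6.7% of the arm.
- Withdrawn when the window lapses: 42 − 17 = 25 days; 25/42 = 60%; 25/420 = 6.0% of the arm.

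**Same count for other visits, on the schedule's listed days** (planned day, then window lapse 3 days later)

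| Visit | Day | Days lost | Share of 420 |
|---|---|---|---|
| 2 | 7 | 35 to 32 | 8.3% to 7.6% |
| 3 | 14 | 28 to 25 | 6.7% to 6.0% |
| 4 | 28 | 14 to 11 | 3.3% to 2.6% |
| 5 | 35 | 7 to 4 | 1.7% to 1.0% |

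On a strict weekly calendar, Visit 4 falls on Day 21 (21 to 18 days, 5.0% to 4.3%) and Visit 5 on Day 28 (14 to 11 days, 3.3% to 2.6%).

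**Visits**

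After a withdrawal at Visit 3, 10 − 3 = 7 scheduled visits are not held as planned. One of them, the final visit, may be brought forward.

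**The case against.** The strongest answer is that the section can be read without conflict, in either of the two ways set out above, and that nobody has to be withdrawn. This largely stands. A reader might infer a flat contradiction, or that every long infection pause ends in withdrawal. The documents support neither. The wording is ambiguous, withdrawal is permissive, and skipping an application while staying in the trial is not prohibited. Infection is not among the possible reasons for discontinuation listed in section 3, and the withdrawal sentence may also serve participants who cannot tolerate the rinse.

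A reader might also infer that safety follow-up stops altogether. It does not. The infection is noted before any withdrawal and, if recorded as an adverse event, is followed to resolution or stability. A final visit is sought. What is lost is new events after a ten-minute topical rinse has been stopped, and the Risk/Benefit Assessment regards systemic effects as highly unlikely.

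The infection percentages in the Introduction (more than 50% of foot wounds, of which more than 25% chronic or relapsing) might be used to predict how many participants would be lost. They carry no time frame, and the exclusion criteria remove moderate-to-severe infection, recent intravenous antibiotics and osteomyelitis. They make deferral plausible but do not size it.

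Finally, it is tempting to say that any late return pushes the last application beyond Day 42. A pause of up to 3 days from the planned day fits the window and need shift nothing, and Visit 6 may in any case fall as late as Day 42 + 3 = 45.

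One part of the concern survives these answers. The section does not say which reading applies, and it names no way to stop treatment and remain under observation.

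**Conclusion.** The point holds as an ambiguity with an avoidable risk to the primary safety data. If the withdrawal option is used for a participant deferred at Visit 3, 25 to 28 of 42 days of new-event recording are lost, or 6.0% to 6.7% of one arm's participant-days. The lower figure assumes withdrawal when the window lapses, the higher one withdrawal on the planned day. Both assume that recording stops at withdrawal, as section 5 says, and that the arm has 10 participants.

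The protocol gives no deferral rate and no expected length of infection, so the total loss across the trial cannot be stated. The planned summaries are descriptive, so no test is invalidated. The change is worth making because this is a first-in-human study with small arms, the loss would be tied to infection, and the correction costs little.

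**What to change.** 1. In section 7, Prior to the Application of Treatment, replace "Alternatively, the participant may be withdrawn from the study" with wording such as: *Alternatively, study treatment is discontinued, with scheduled visits and AE recording continued to Week 18 unless consent is withdrawn.*
2. In the same section, replace the open-ended return sentence with one rule. An application not given within its visit window is recorded as missed. Treatment may resume at the next scheduled treatment visit, up to Visit 6, if the infection has settled. Assessments stay on the original Day 0 calendar.
3. In section 3, Withdrawal of Participants from Study, state that inability to tolerate treatment, unacceptable adverse events or infection lead to stopping treatment, not to leaving the study.

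The cost is a few sentences in two sections, with no visits beyond those already scheduled. The downside is that some participants in follow-up will have had fewer than six applications. Section 9, Safety Data, already plans to summarise the number of dressings applied, so incomplete courses will be visible.
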